### **Treatment with praziquantel**

Volunteers will be treated with 60 mg/kg praziquantel at week 8 and at week 12. The treatment will consist of a prespecified number praziquantel 600 mg tablets according to the table in section 7.3. In addition to specific treatment with praziquantel, symptomatic treatment will be administered at the discretion of the attending physician.

Volunteers will not be admitted to the hospital during this study, unless the study doctors or the safety monitoring committee deem it necessary.

### **Safety laboratory evaluation**

During the study, blood samples will be drawn to assess safety of infection. The blood sampling schedule is depicted in the flowchart (figure 3). Safety analysis include:

complete blood count (including automated differential count of white blood cells), erythrocyte sedimentation rate, creatinine, potassium, bilirubin, AF, gGT, AST, ALT.

Biological safety parameters will be measured on plasma or serum samples at the central laboratory of the LUMC. Assessment of successful infection will be performed by serum CAA measurements at the department of Molecular Cell Biology of the LUMC at 8 weeks after exposure to cercariae. Another assessment of CAA levels will be performed at week 20 to confirm cure. If volunteers are not cured after two doses of praziquantel, a third round of treatment will be given and its effect on CAA levels monitored. *Schistosoma mansoni* antigen detection tests will be performed retrospectively on all samples, unless

the investigator, safety monitoring committee or accredited METC requests specific testing of certain samples for clinical judgment of adverse events.

In the case where a safety laboratory assessment is outside the reference range for the laboratory, a decision regarding whether the result is of clinical significance or not shall be made by the investigator and shall be based, in part, upon the nature and degree of the observed abnormality. The assessment may first be repeated for confirmation. In all cases, the investigator will document in the source documents, the clinical considerations (i.e., result was/was not clinically significant and/or medically relevant) in allowing or disallowing the subject to continue in the study. Since elevated eosinophils are an expected result of this study this measure will not be marked as abnormal in the eCRF. The maximum amount of blood drawn is 560 ml for the 20 weeks study period.

### **Serology, toxicology, pregnancy test**

A serum sample will be obtained at screening to test for the presence of HIV antigen and antibodies, hepatitis B surface antigen, anti-Hepatitis C antibodies.

A midstream urine sample (approx. 30 ml) will be obtained at the screening visit, in order to avoid contamination with epithelial cells and sediments, to allow proper assessments of amphetamines, cocaine and a commercially available hCG urine test.

### **Source data**

All data collected by the investigator is reported in electronic case report forms. These forms, together with the investigator's notes are considered source data. In case of adverse events/reactions resulting in a medical consultation or hospitalization a medical file can be made. In this case the medical file will be considered as the source data. The diaries, produced by the study volunteers are also considered source data. They will be kept as source documents in the investigator clinical file.

### **Recording of adverse events**

Signs and symptoms will be recorded at all visits and whenever a trial volunteer reports signs or symptoms to the trial physician between visits. The following signs and symptoms will be solicited at all visits: itching, fever (by examination), rash, urticaria, headache, fatigue, malaise, coughing, myalgia, arthralgia, night sweats, back pain, anorexia, nausea, vomiting, abdominal pain, diarrhoea.

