### Main study parameters/endpoints:

Main study parameter/endpoint:

- Frequency and severity of adverse events after controlled human *Schistosoma mansoni* infection with female cercariae

- The number of female cercariae at which 100% volunteers show detectable *Schistosoma mansoni* circulating anodic antigen

Other study parameters/endpoints:

- Time to positive serum and urine CAA test
- Comparison of the peak serum CAA concentration in different dose groups
- Humoral (antibody) response directed against *Sm* antigens
- Cellular responses directed against *Sm* antigens
- Changes in microbiome after controlled human *Schistosoma mansoni* infection with female *Sm* cercariae

**Nature and extent of the burden and risks associated with participation, benefit and group relatedness:** Volunteers will be requested to visit the trial centre on a weekly basis for 16 weeks. After this bi-weekly visits will follow until week 20. Final follow up visit will be after one year. Blood and urine sampling will take place at every visit. Nasosorption sampling is performed during the first eight weeks. They will keep a diary to record adverse events during 20 weeks. Volunteers will be dermally exposed to female cercariae once. They may experience adverse events, related to acute schistosomiasis syndrome with fatigue, malaise, and fever. At 8 weeks and 12 weeks after infection, they will be treated with praziquantel to cure the *Schistosoma* infection. Praziquantel is known to potentially give fatigue, gastrointestinal side effects, and dizziness. There is no benefit to participation in the trial.

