## 7. NON-INVESTIGATIONAL PRODUCT: praziquantel

### 7.1 Name and description of non-investigational product(s)

#### Praziquantel

All volunteers will be treated with 60 mg/kg praziquantel at week 8 and week 12 after infection. Praziquantel is the only drug registered for the treatment of schistosomiasis. Cure rates with a single dose of 40 mg/kg has been reported to vary between 40-90% [4, 5] in endemic areas, however in travelers the efficacy appears lower [14] which may be caused by lower infection intensity or differential host-immune responses. Therefore, repeated praziquantel doses may be required to achieve full cure. A common side effect of praziquantel (>10%) is fatigue. Other less common side effects are abdominal discomfort, nausea, and dizziness. For a summary of findings from non-clinical and clinical studies, please refer to the “bijsluiter” (SPC Praziquantel). Praziquantel has been described to temporarily impair skilled tasks, and thus volunteers treated with praziquantel will be advised not to drive a car or operate machinery on the day of treatment with praziquantel and the day thereafter [15]. They are instructed to take praziquantel after a meal preferably containing high-fat, and high carbohydrate content [16].

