A flu-like syndrome with protracted low to medium grade fever, fatigue, myalgia, malaise, non-productive cough, eosinophilia and patchy infiltrates on chest radiography can occur. Because it is unclear whether an acute schistosomiasis syndrome is related to the number of infected schistosomes or oviposition, it is hard to predict the chances of Katayama fever occurring and in which dose group. In the CoHSI1 study, two volunteers (out of three) in the 30 cercariae dose group developed symptoms of an acute schistosomiasis syndrome [11] that resolved without treatment. Another two (out of 11) in the 20 cercariae dose group developed severe AEs suggestive acute schistosomiasis syndrome [11]. In severe cases the syndrome can be treated symptomatically with analgesics, NSAIDs and corticosteroids.

c. Morbidity related to oviposition

Eggs trapped in the intestines or liver can induce a granulomatous host immune response that may present as abdominal pain, diarrhoea, and rectal

bleeding. The frequency of these symptoms is positively associated with the infection intensity. In severe cases, chronic inflammation may lead to periportal fibrosis resulting in clinical symptoms observed in individuals with portal hypertension, such as hepatomegaly, ascites, or oesophageal varices. The time between initial infection and these advanced stages are approximately 5-15 years [19]. In contrast to the male-only infections where egg production was never reported, we and others have in rare occasions observed egg-production in single-sex female infection of mice [20]. The numbers of eggs recovered were substantially lower as compared to mixed infections (please also see paragraph 13.1) and were never found to contain a viable miracidium. Possibly, the single female can produce and secrete egg shells on rare occasions. To reduce the possible production and number of egg(shells) we have adjusted the dose schedule to as low as possible doses of female cercariae and will initiate treatment as soon as the worm reaches adulthood and is possibly capable of producing eggs.

d. Acute toxemic neuroschistosomiasis

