Neurological symptoms, such as low back pain irradiating to the limbs, lower limb muscle weakness, paresthesia, acute encephalitis, encephalomyelitis, aseptic meningitis are rare complications of schistosomiasis and thought to occur as a consequence of an inflammatory response of the host against the *Schistosoma* eggs deposited in the central nervous system by ectopic worms. Given the fact that this complication, even in endemic areas where worm burden is high, is rare, it is highly unlikely to happen after infection with female *Schistosoma mansoni* only.

2. Risks related to treatment with praziquantel

Please refer to section 2.3.2.2. of the Product Dossier for an extensive description of the available treatment options. In summary, praziquantel is the only registered, extremely safe and highly effective drug for the treatment of *Schistosoma mansoni* infections. Because it is active on the mature worms only, treatment is recommended from 2-3 months after infection. Praziquantel is extremely safe with no long-term toxicity also for infants and pregnant women [6, 21, 22]. The short-term side effects are primarily fatigue, malaise, gastro-intestinal side effects and dizziness (see SPC Praziquantel) which are directly correlated with the pre-treatment intensity of infection [22]. Because of the risk of dizziness, volunteers are advised not to drive a car or operate machinery for the day of treatment and the day thereafter. In very rare instances, allergic reactions have been reported [22].

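### The symptoms solicited at every visit leave out dizziness, a named effect of a drug every volunteer takes twice, and rectal bleeding, so these two may be under-recorded relative to the listed symptoms

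*Protocol*

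**What the plan says.** Section 8.3, Recording of adverse events, gives a closed list of symptoms to be asked about at all visits. It opens "The following signs and symptoms will be solicited at all visits: itching, fever (by examination), rash, urticaria, headache, fatigue, malaise" and continues "coughing, myalgia, arthralgia, night sweats, back pain, anorexia, nausea, vomiting, abdominal pain, diarrhoea".

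Dizziness is named as a praziquantel effect in three places:

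- Summary, on burden and risks: "Praziquantel is known to potentially give fatigue, gastrointestinal side effects, and dizziness".
- Section 7.1: "Other less common side effects are abdominal discomfort, nausea, and dizziness".
- Section 11.3: "The short-term side effects are primarily fatigue, malaise, gastro-intestinal side effects and dizziness". The same paragraph adds: "Because of the risk of dizziness, volunteers are advised not to drive a car or operate machinery".

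Sections 7.1 and 8.3 give praziquantel to every volunteer at week 8 and again at week 12.

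Rectal bleeding appears once, in 11.3 under morbidity related to oviposition. The sentence "Eggs trapped in the intestines or liver can induce a granulomatous host immune response that may present as abdominal pain, diarrhoea, and rectal" ends, after a page break, with the word bleeding.

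The occurrence and severity of adverse events is one of the two main endpoints (8.1.1). Section 10.1.1 analyses it by tabulating every adverse event per volunteer and by giving, for each group, the proportion of volunteers with mild, moderate and severe events.

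**The concern.** A symptom asked about by name at every visit is ascertained differently from one that is recorded only when somebody mentions or notices it. Section 10.1.1 puts both kinds into one tabulation. If a symptom that the protocol itself names as a risk is left off the prompt list, its frequency may come out low beside those of the prompted symptoms, and a reader of the table could take the difference as real.

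Dizziness is the stronger case. All volunteers take the drug twice, and 11.3 thinks the effect important enough to restrict driving on the treatment day and the day after. The next scheduled visits are a week after each round, at weeks 9 and 13, so a brief unprompted symptom is easily forgotten.

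Rectal bleeding is the weaker case because the protocol thinks it very unlikely. Even so, 13.1(b) says egg-related symptoms are a small risk that the male-only infection did not carry, and that female-only infection has not been done in humans before. The two other symptoms given for that complication are already solicited.

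**Working it through.** This is a comparison of texts. The protocol states no figure that could be reproduced.

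**Step 1. Count the list.** The first part of the 8.3 list has 7 items (itching, fever, rash, urticaria, headache, fatigue, malaise) and the second has 10 (coughing to diarrhoea): 7 + 10 = 17. Dizziness is 0 of 17 and rectal bleeding 0 of 17.

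**Step 2. Match the named effects to the list.**

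| Effect | Named in | Solicited item in 8.3 |
|---|---|---|
| Praziquantel: fatigue | Summary, 7.1, 11.3 | fatigue |
| Praziquantel: malaise | 11.3 | malaise |
| Praziquantel: nausea | 7.1 | nausea |
| Praziquantel: abdominal discomfort, gastrointestinal effects | Summary, 7.1, 11.3 | abdominal pain, nausea, vomiting, diarrhoea |
| Praziquantel: dizziness | Summary, 7.1, 11.3 | none |
| Eggs: abdominal pain | 11.3 | abdominal pain |
| Eggs: diarrhoea | 11.3 | diarrhoea |
| Eggs: rectal bleeding | 11.3 | none |

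Section 11.3 also mentions very rare allergic reactions to praziquantel; itching, rash and urticaria cover part of these. Dizziness is therefore the only usual praziquantel effect with no solicited item, and rectal bleeding the only one of the three egg-related symptoms.

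**Step 3. See how the two would still be recorded.** Section 9.2.1 records events that the subject reports or that staff observe. Section 9.2.4 puts solicited and unsolicited events in the case report form. Section 8.3 asks for a diary of adverse events up to week 20, which spans both praziquantel days, and asks volunteers to report any grade 2 or 3 event to a physician available at all hours. So the events are not lost by design. What differs is the prompting at visits. The diary form is not shown, so whether it prompts for these symptoms is unknown.

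**Step 4. Check whether a decision depends on it.** Escalation depends on serum CAA positivity, subject to the safety committee's advice (section 3, 9.5). The numerical stopping rule in 8.7 counts infection-related grade 3 events that stay at grade 3 for more than 48 hours, and 9.2.5 grades causality against the cercariae. Transient dizziness after praziquantel does not enter it. A severe bleed would fall under the instruction to report grade 2 and 3 events.

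**Step 5. Illustrate the size for dizziness.** This rests on assumptions. Section 7.1 places fatigue above 10% and calls dizziness less common. Assume a per-round probability q of 2%, 5% or 10%, independence between the two rounds, and 10 volunteers at a dose. The expected number with dizziness at least once is 10 × (1 − (1 − q)²):

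- q = 0.02: 10 × (1 − 0.9604) = 0.40
- q = 0.05: 10 × (1 − 0.9025) = 0.98
- q = 0.10: 10 × (1 − 0.81) = 1.90

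If unprompted recording caught half of what prompting would catch, the expected shortfall would be 0.20, 0.49 or 0.95 volunteers in 10. None of these rates, nor the one-half, stands in the protocol. No comparable illustration is possible for rectal bleeding, for which the protocol gives no rate.

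**The case against.** The strongest reply is that nothing in the protocol contradicts itself. The endpoint has no list of components: it covers all adverse events. The list in 8.3 is a set of visit prompts, and 7.1 and 11.3 are descriptions of risk; no rule says that the first must reproduce the second. This stands. A reader might infer that the safety endpoint is defined differently in different places, and the text does not support that.

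A reader might also infer that the two symptoms are recorded only if the volunteer brings them up. That goes too far, given staff observation and the 20-week diary.

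Nor is rectal bleeding an expected effect. Section 11.3 says only that egg morbidity may present this way, and 13.1 rates the risk as extremely small (a) and low (i). Eggs are also looked for by PCR at week 8 and by repeated egg ELISA. These tests reduce the concern, but they do not record symptoms.

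It is tempting to add that a zero count of unsolicited rectal bleeding could not support the extremely small rating. The protocol draws no such inference: its rating is made beforehand, from mouse egg counts and host size. Perfect prompting would not change this either. With 0 of 10, the exact one-sided 95% upper limit is 1 − 0.05^(1/10) = 26%, and the upper end of the two-sided interval is 1 − 0.025^(1/10) = 31%.

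Finally, the effect on the main summary is slight. A missed dizziness changes the proportion with an event of a given grade only if the volunteer had no other event of that grade, and 13.1(i) expects adverse effects in nearly everyone. All dose groups receive the same praziquantel regimen, so there is no evident reason for the fraction captured to differ by dose. This also stands. It bears on the overall proportions more than on the symptom-by-symptom frequencies, where the gap remains.

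**Conclusion.** The point holds as a modest gap in ascertainment. Two symptoms that the protocol names as risks are missing from the list it fixes for every visit. They would be recorded, but less systematically than the 17 listed symptoms, so their tabulated frequencies may be understated by comparison. The case is clear for dizziness. It is weaker for rectal bleeding and rests there on consistency, since the other two symptoms of the same complication are solicited.

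The size cannot be derived from the document. On the assumed rates above, the shortfall for dizziness is below one volunteer in 10. The conclusion assumes that unprompted recording is less complete than prompted recording, and that the diary does not already prompt for these two symptoms. If it does, the gap is smaller still. No escalation or numerical stopping rule is affected.

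**What to change.** In section 8.3, Recording of adverse events, add dizziness to the symptoms solicited at all visits, and also rectal bleeding. If the diary prompts by symptom, add both there. If the sponsor prefers to leave either unsolicited, one sentence giving the reason would do.

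The cost is two lines on the visit form and possibly the diary, and a few more mild events recorded. The male study's solicited list is not given here; if that study did not solicit these items, no like-for-like male-female comparison on them is possible. The change is best made before the first exposure. If it comes later, these two items should not be compared between groups questioned with and without the added prompts.

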### **Exploratory immunology and metabolomics**

The overall objective is to find immunological or metabolic markers that associate with female *Schistosoma mansoni* infection. The sampling schedule is depicted in the flow chart below (figure 3).

Humoral assessment will include antibody assays by immunofluorescence, ELISAs and arrays for specific *Schistosoma mansoni* proteins or glycans.

Cellular assessment of parasite-specific (subset) T cell responses, will be conducted by multi-parameter flow cytometry, cyTOF and ELISPOT assays with or without using Sm-specific *in vitro* stimulation.

The metabolic profile of serum and urine samples will be evaluated at timepoints before, during and after infection.

An analysis of faecal samples to investigate the gut microbiome will be performed at 7 timepoints during the trial.

During the first 8 weeks of infection, nasal lining fluid will be collected by 2 min nasosorption in a matrix strip (Nasosorption™, Hunt Developments) and frozen at -80°C. This is a non-invasive procedure. After thawing, various immune parameters can be measured by multiplex platforms, like Luminex or Proseek (Olink). Nasal metabolomics can also be performed.

#### **8.4 Withdrawal of individual subjects**

Subjects can leave the study at any time for any reason if they wish to do so without any consequences. However, for safety purposes volunteers will be required to complete some follow-up visits to monitor treatment. The investigator can decide to withdraw a subject from the study for urgent medical reasons.

#### **8.5 Replacement of individual subjects after withdrawal**

Subjects will be replaced after withdrawal, if a subject withdraws from group A of 3 volunteers. In that case, the second group from the same dose will increase to 8 volunteers.

#### **8.6 Follow-up of subjects withdrawn from treatment**

If a subject fails to appear for a follow-up examination, extensive effort (i.e. documented phone calls and certified mail) will be undertaken to locate or recall him or at least to determine his health status. These efforts will be documented in the source documents. In the event that a volunteer discontinues the study for any reason, he/she will be urged to complete all safety follow-up, including treatment with praziquantel.

Figure 3. Flow chart

|                                              | Screening        | Challenge      | Follow up |    |    |    |    |    |    |                |     |     |     |     |     |     |     |     |     |     |         |  |
|----------------------------------------------|------------------|----------------|-----------|----|----|----|----|----|----|----------------|-----|-----|-----|-----|-----|-----|-----|-----|-----|-----|---------|--|
| Deviation                                    |                  |                | 3 days    |    |    |    |    |    |    |                |     |     |     |     |     |     |     |     |     |     | 4 weeks |  |
| Visit                                        |                  | V1             | V2        | V3 | V4 | V5 | V6 | V7 | V8 | V9             | V10 | V11 | V12 | V13 | V14 | V15 | V16 | V17 | V18 | V19 | V20     |  |
| Week                                         |                  | 0              | 1         | 2  | 3  | 4  | 5  | 6  | 7  | 8              | 9   | 10  | 11  | 12  | 13  | 14  | 15  | 16  | 18  | 20  | 52      |  |
|                                              |                  |                |           |    |    |    |    |    |    |                |     |     |     |     |     |     |     |     |     |     |         |  |
| Obtain informed consent                      | X                |                |           |    |    |    |    |    |    |                |     |     |     |     |     |     |     |     |     |     |         |  |
| Clinical evaluation                          | X                | X              | X         | X  | X  | X  | X  | X  | X  | X              | X   | X   | X   | X   | X   | X   | X   | X   | X   | X   | X       |  |
| Exposure to cercariae                        |                  | X              |           |    |    |    |    |    |    |                |     |     |     |     |     |     |     |     |     |     |         |  |
| Praziquantel (60 mg/kg)                      |                  |                |           |    |    |    |    |    |    | X              |     |     |     | X   |     |     |     |     |     |     |         |  |
| Eosinophils                                  |                  |                |           | X  |    | X  | X  | X  | X  |                |     | X   |     | X   |     | X   |     | X   | X   | X   | X       |  |
| Safety tests                                 | X  | X  |           |    |    |    |    |    |    | X  |     |     |     |     |     |     |     |     |     |     |         |  |
| Urine pregnancy test for female volunteers   | X                | X              |           |    |    |    |    |    |    |                |     |     |     |     |     |     |     |     |     |     |         |  |
| UCP CAA (serum)                              | X                | X              | X         | X  | X  | X  | X  | X  | X  | X              | X   | X   | X   | X   | X   | X   | X   | X   | X   | X   | X       |  |
| UCP CAA (urine)                              |                  | X              | X         | X  | X  | X  | X  | X  | X  | X              | X   | X   | X   | X   | X   | X   | X   | X   | X   | X   | X       |  |
| Schistosomiasis serology: worm IFA           | X                |                |           |    |    | X  | X  | X  | X  | X              |     |     |     | X   |     |     |     | X   |     | X   | X       |  |
| Schistosomiasis serology: egg ELISA          | X                |                |           |    |    | X  |    |    |    | X              |     |     |     | X   |     |     |     | X   |     | X   | X       |  |
| Schistosomiasis PCR eggs                     |                  |                |           |    |    |    |    |    |    | X              |     |     |     |     |     |     |     |     |     |     |         |  |
| Immunological assays (antibody and cellular) |                  | X              |           |    |    | X  |    |    |    | X              |     |     |     | X   |     |     |     | X   |     | X   | X       |  |
| Metabolomics                                 | X                | X              | X         | X  | X  | X  | X  | X  | X  | X              | X   | X   |     | X   |     | X   |     | X   | X   | X   | X       |  |
| Microbiome                                   |                  | X              |           |    |    | X  |    |    |    | X              |     |     |     | X   |     |     |     | X   |     | X   | X       |  |
| Nasosorption                                 |                  | X              | X         | X  | X  | X  | X  | X  | X  | X              |     |     |     |     |     |     |     |     |     |     |         |  |

1: HIV, HBV, HCV, urine cocaine and amphetamines

2: automated CBC, ESR, creatinine, BUN, sodium, potassium, bilirubin, AF, γGT, AST, ALT, glucose

